## Abstract

**Background:**

Liver cirrhosis, the advanced stage of many chronic liver diseases, is associated with escalated risks of liver-related complications like decompensation and hepatocellular carcinoma (HCC). Morbidity and mortality in cirrhosis patients are linked to portal hypertension, sarcopenia, and hepatocellular carcinoma. Although conventional cirrhosis management centered on treating complications, contemporary approaches prioritize preemptive measures. This study aims to formulate novel blood- and imaging-centric methodologies for monitoring liver cirrhosis patients.

**Methods:**

In this prospective study, 150 liver cirrhosis patients will be enrolled from three Swedish liver clinics. Their conditions will be assessed through extensive blood-based markers and magnetic resonance imaging (MRI). The MRI protocol encompasses body composition profile with Muscle Assement Score, portal flow assessment, magnet resonance elastography, and a abbreviated MRI for HCC screening. Evaluation of lifestyle, muscular strength, physical performance, body composition, and quality of life will be conducted. Additionally, DNA, serum, and plasma biobanking will facilitate future investigations.

**Discussion:**

The anticipated outcomes involve the identification and validation of non-invasive blood- and imaging-oriented biomarkers, enhancing the care paradigm for liver cirrhosis patients. Notably, the temporal evolution of these biomarkers will be crucial for understanding dynamic changes.

**Trial registration:**

Clinicaltrials.gov, registration identifier NCT05502198. Registered on 16 August 2022. Link: https://classic.clinicaltrials.gov/ct2/show/NCT05502198.

## Background

Chronic liver diseases affects approximately 1 billion individuals worldwide and causes an estimated 2 million deaths annually [1]. The most common causes of liver-related mortality are chronic hepatitis B, chronic hepatitis C, alcohol-related liver disease and non-alcoholic fatty liver disease (NAFLD) [2, 3]. The end stage of all chronic liver diseases is liver cirrhosis, which entails an increased risk of liver-related complications such as decompensation and hepatocellular carcinoma (HCC).

The transition from chronic liver disease to cirrhosis involves inflammation, fibrogenesis and vascular occlusion causing microvascular changes with sinusoidal remodelling, formation of intrahepatic shunts, and hepatic endothelial dysfunction [4]. This causes increased hepatic resistance and splanchnic vasodilatation which precipitates and exaggerates portal hypertension – the underlying pathophysiological cause of liver decompensation.

The gold standard for estimating and diagnosing portal pressure is hepatic venous pressure gradient (HVPG) – an invasive examination. However, clinical, radiological, and endoscopic signs of decompensation is more commonly used to estimate the severity of the portal pressure – which is highly associated with mortality (ranging from 1 to 60% depending on decompensating events). However, recent studies have shown that non-invasive evaluation of portal pressure and flow with magnetic resonance (MR) imaging (MRI) highly correlates with HVPG, and 7-year follow-up of spleen volume (using CT) have shown strong links to decompensation and HCC occurrence [5, 6].

Beyond the lethality of decompensation, liver cirrhosis also entails an increased risk of developing HCC [7]. If diagnosed early, when the tumor is still small, most patients can receive curative treatment. Therefore, current guidelines recommend screening for HCC biannually with ultrasonography, computed tomography or MRI, where the most common used modality is ultrasonography [8]. However, recent studies have found MRI to have a higher HCC detection rate compared to ultrasound [9], with abbreviated MRI (aMRI) showing high sensitivity for detecting HCC irrespective of protocol or any contrast agent [10].

Sarcopenia, a multifactorial muscle disease typically defined as loss of skeletal muscle mass and function, has gained increased attention in the field of liver cirrhosis during the last decade. In chronic disease, sarcopenia is a progressive disorder associated with adverse outcomes (e.g. falls, fractures and physical disability) and increased mortality and morbidity, especially in elderly patients [11]. In patients with cirrhosis, sarcopenia is present in approximately 40–60%, and associated with increased morbidity and mortality, increased ICU length of stay and poorer treatment results, recognizing sarcopenia as a prognostic risk factor in cirrhosis [11–13]. Recent clinical guidance recommends systematic assessment of sarcopenia in patients with cirrhosis, both for liver transplant decision-making as well as monitoring in those with decompensated cirrhosis undergoing management for sarcopenia [14]. Magnetic resonance imaging is considered the gold standard for body composition assessment, and methods for objective measurement of muscle health unbiased by BMI has been developed, such as the Muscle Assessment Score (MASs) [15]. The components of MAsS, i.e.*,* thigh fat-free muscle volume z-score (FFMVz) and thigh muscle fat index (sex-adjusted MFI), have been shown to be an independent predictor of all-cause mortality and identifies vulnerable patients with fatty liver disease [16, 17].

The field of liver cirrhosis is shifting from being reactive (i.e., treating decompensation once it occurs) to being proactive (i.e.*,* preventing decompensation from happening). For this shift to be successful, we need validated biomarkers that predict prognosis and is reflective of change in disease activity. The aim of the current study is to test blood and imaging-based biomarkers to improve outcome for patients with liver cirrhosis by detecting those patients at risk of developing HCC, sarcopenia, and decompensating events.

Therefore, in this prospective cohort study we aim to recruit patients with cirrhosis undergoing HCC-screening, utilising MRI instead of ultrasonography for repeated imaging every 6 months for 2 years, to investigate the development of HCC, liver stiffness, and development of portal hypertension as wells as body composition profiling including MAsS for detecting sarcopenia. We will assess these aspects with a single, short, clinically feasible, 20 min MR-examination, together with extensive blood sampling for building a biobank for future analyses.

## Methods/design

### Overview

ACCESS-ESLD (A Rapid, Non-invasive, Clinical Surveillance for CachExia, Sarcopenia, Portal HypertenSion, and Hepatocellular Carcinoma in End-Stage Liver Disease) is a multi-center prospective cohort study aiming to include 150 patients with liver cirrhosis. Patients with established liver cirrhosis will be included and repeated abbreviated MR-examinations will be performed instead of ultrasonography at baseline, 6 months, 12 months, and 18 months, i.e., with a 6-month interval. This interval is currently recommended and used in normal clinical care for surveillance of HCC in these patients. The MR-examination will include body composition profiling (BCP; for e.g.*,* sarcopenia [via MAsS] and portal hypertension [via spleen volume]) and HCC-screening. Patients will be consecutively enrolled at the department of Gastroenterology and Hepatology, University Hospital in Linköping, County Hospital in Jönköping (Ryhov) and District Hospital in Eksjö (Höglandssjukhuset). A detailed medical history as well as a comprehensive list of clinical data, biochemical investigation, tests of physical function and mobility, and biological samples will be obtained in all individuals.

### Objectives

The purpose is to identify risk factors as well as biomarkers of present disease severity and future risk of liver-related clinical events in patients with liver cirrhosis. We aim to do this by characterizing body composition profiling, portal blood flow, liver stiffness, and spleen volume.

#### Primary aim

To determine if cross-sectional or temporal changes in FFMV and MFI (i.e.*,* MAsS), in combination or as individual factors, predict the development of ESLD-related events (i.e., decompensation, HCC and sarcopenia) or worsening of liver function (i.e.*,* Model for End-Stage Liver Disease [MELD] score and Child-Turcotte-Pugh score [CTP]).

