**Fig. 3 Fig3:**
[figure not shown]
An example of clinical report for body composition profiling (AMRA® Profiler 4 MAsS Scan), including whole-body water-fat separated imaging examples (bottom left), the muscle assessment score (MAsS; blue region of the report) which are the biomarkers used in the primary aim to assess sarcopenia, as well as measurements of abdominal adiposity (bottom right)

The MR-protocol is efficiently condensed, and the MR data will be acquired within c. 20 min.

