Therefore, in this study recruited patients with cirrhosis will undergo HCC-screening, utilising MRI instead of ultrasonography, biannually, for 2 years – investigating both the presence of HCC and biomarkers associated with ESLD, such as sarcopenia and associated morbidities. Methodologically, we will assess sarcopenia, clinically significant portal hypertension, liver stiffness and HCC with a single short MR-examination. Sarcopenia will be assessed using BCP with MAsS. The BCP analysis is acquired with a 8 min neck-to-knee MR-examination which will also provide measurements of abdominal fat compartments and spleen volume [21, 53]. We will also measure L3-SMI which previously has been used on computed tomography for measuring sarcopenia and compare the predictive performance against MAsS. Liver stiffness will be assessed by Fibroscan™ and standard clinical MRE methods. HCC screening will be performed using so-called abbreviated MRI (aMRI).

A major strength of our study is that included patients undergo same-day examinations allowing for accurate comparisons between the results of different tests and modalities utilized. Another strength is that it is a longitudinal study repeating the same investigations over a 2-year period as well as an extra visit after the last scheduled visit for all patients who experience decompensation. This allows us to follow the natural history of cirrhosis and investigate how imaging and other biomarkers relate to actual clinical outcomes i.e.*,* decompensation, HCC, and sarcopenia.

During an era where non-invasive test (NIT) proves to be non-inferior or even superior to invasive, diagnostic interventions often entitled as gold standard, the need for implementing, validating, and further evolving available non-invasive biomarkers in prospective cohorts are crucial. Albeit VCTE and NITs have revolutionized the field of hepatology – their strength mainly lies in their high negative predictive values. However, albeit, VCTE has recently shown to match the prognostic capability as histological fibrosis stage, it has some limitations – the main one being its inability to also screen for HCC.

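### For the sarcopenia event in the primary aim, predictor (FFMV/MFI, i.e. MAsS) and outcome come from the same thigh MRI measurement, so part of any association is built in

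*Protocol article*

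**What the plan says.** Under Primary aim, the predictors are cross-sectional values of, or temporal changes "in FFMV and MFI (i.e.*,* MAsS), in combination or as individual factors". They are to "predict the development of ESLD-related events (i.e., decompensation, HCC and sarcopenia"), "or worsening of liver function" as measured by MELD and CTP.

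Four places say how sarcopenia is assessed, and all name MAsS:

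- Background, last paragraph: "body composition profiling including MAsS for detecting sarcopenia".
- Overview, on the content of the MR examination: "sarcopenia [via MAsS] and portal hypertension [via spleen volume"].
- Fig. 3 caption, on the MAsS part of the report: "which are the biomarkers used in the primary aim to assess sarcopenia".
- Discussion: "Sarcopenia will be assessed using BCP with MAsS".

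The Background gives the components of MAsS as the thigh FFMV z-score and sex-adjusted thigh MFI. Hand grip strength, the Short Physical Performance Battery (SPPB) and the Liver Frailty Index (LFI) are also collected, and Table 3 schedules muscle function testing at every visit. The skeletal muscle index at L3 (L3-SMI) is measured too. None of these is named as the criterion for the sarcopenia event; the Discussion gives L3-SMI the role of a rival predictor to MAsS.

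**The concern.** A marker tested against an event defined by the same marker will show an association whether or not it carries information about the disease. Patients whose baseline FFMV lies just above a cut-off need only a small fall, or only scan noise, to be counted as new cases. If the predictor is change in FFMV, the follow-up scan can enter both the predictor and the event.

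At stake is what a positive result would mean. A finding that MAsS predicts sarcopenia could be reported as prognostic evidence when it shows only that a low thigh measurement tends to remain low or be followed by a lower one. The sample-size section calls sarcopenia one of the main objectives, so this component is likely to be prominent in the report.

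**Working it through.** The plan gives no figure for predicting sarcopenia. Its sample-size calculation concerns detecting a change in muscle volume, so there is no planned number to reproduce. The check is one of definitions, followed by an illustration of size.

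**Definitions.**

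1. Predictor: FFMV and MFI, equated with MAsS (Primary aim).
2. MAsS: thigh FFMV z-score and sex-adjusted thigh MFI (Background).
3. Event: sarcopenia, assessed by MAsS (Background, Overview, Fig. 3 caption, Discussion).
4. From 1 to 3, predictor and event are functions of the same two thigh quantities.

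**Why earlier measurement of the predictor does not remove the problem.** Write M₀ for the baseline value, M₁ for a follow-up value, D = M₁ − M₀ for the change and c for a cut-off. A patient with M₀ > c becomes a case when M₁ ≤ c, that is, when M₀ + D ≤ c. On that scan the event is fully determined by M₀ and D, which are the two forms of predictor in the primary aim.

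**Illustration of size.**

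From the protocol: n = 150; scans at 0, 6, 12 and 18 months; scan coefficient of variation 0.8–1.5%; prevalence of sarcopenia 30–70% in imaging studies (the last two from the sample-size section).

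Assumed, not in the documents: between-person SD of FFMV 10–20%; one FFMV cut-off placed to give the stated prevalence at baseline; no true change in anyone; MFI not modelled.

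At risk: baseline scan above the cut-off. Event: a follow-up scan at or below it.

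| Predictor | AUC for new sarcopenia |
|---|---|
| Baseline FFMV | about 0.91–0.99 |
| 0–18-month change in FFMV | about 0.67–0.70 |
| Value for an unrelated outcome | 0.50 |

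At the 1.5% coefficient of variation this yields about 4–9 new cases per study, all produced by scan noise.

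A second set-up used a z-score with mean −0.5 and SD 1, cut-off −1, measurement error SD 0.1 and a single follow-up scan. All of these are assumptions.

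- No true change: AUC 0.97 for baseline and 0.86 for change, in runs with at least two events.
- True change with mean −0.3 and SD 0.4: AUC 0.89 and 0.82.
- An unrelated outcome of equal frequency: about 0.50, with about 5–6% of tests significant.

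The two figures for change (0.67–0.70 and 0.86) differ mainly because of the event rule. In the second set-up one follow-up scan defines both the change and the event; in the first, a crossing at 6 or 12 months also counts. The size depends on such choices; the direction does not.

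**The case against.** The strongest reply is that the article never sets a formal criterion or cut-off for the sarcopenia event. The Background, Overview and Discussion sentences can be read as describing what the MR examination measures, and the Fig. 3 caption as naming the predictor. The Discussion also lists sarcopenia among the clinical outcomes to which imaging markers will be related, and event definitions are often left to the full protocol or analysis plan.

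The missing cut-off is conceded and is not the complaint. The article does state the method of assessment, four times, and it is always the predictor. The caption ties it to the primary aim. An analysis plan that follows this text inherits the overlap.

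It is also fair that the illustration is not a model of the trial. It uses one component of MAsS, assumed SDs and no true change. The high baseline AUC mainly reflects closeness to a threshold, which is real prediction of the marker by itself but says nothing about liver events.

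A reader might infer four stronger points, which the documents do not support:

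- *A composite event is contaminated.* No pooled analysis is stated. The phrase about combination refers to the predictors.
- *The comparison of MAsS with L3-SMI is tilted.* The Discussion does not say on which outcome they will be compared. The tilt arises only if that outcome is MAsS-assessed sarcopenia.
- *Function tests are excluded from the outcome.* No passage excludes them; the article only does not name them as the criterion.
- *Only 60–90 of 150 patients can develop sarcopenia.* That applies a background figure ("In patients with cirrhosis, sarcopenia is present in approximately 40–60" per cent) with no stated link to a MAsS cut-off. The sample-size section's 30–70% would give 150 × 0.30 = 45 to 150 × 0.70 = 105. A reduced risk set is in any case ordinary in an incidence analysis.

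**Conclusion.** The point holds for one component of the primary aim. As written, FFMV/MFI are tested as predictors of an event whose only stated assessment is FFMV/MFI, so an association for that event is partly built in. Under the stated assumptions, with no muscle change at all, the AUC is about 0.91–0.99 for baseline FFMV and 0.67–0.70 for its change, where an unrelated outcome would give 0.50. These values illustrate the mechanism and do not forecast the trial's results; the conclusion itself rests on the definitions alone.

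It would be wrong to conclude that the whole primary aim is circular. Decompensation, HCC and worsening of MELD or CTP are not measured by MAsS, and results for them remain interpretable.

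**What to change.** 1. Remove MAsS-assessed sarcopenia from the events against which FFMV, MFI and MAsS are tested. The primary aim is then judged on decompensation, HCC and MELD/CTP worsening.
2. Report MAsS-assessed sarcopenia descriptively only, and state that it will not be pooled with those events.
3. If sarcopenia or frailty is kept as a predicted outcome, make it secondary and base it on measures that do not use thigh FFMV or MFI. Hand grip strength, SPPB and LFI are already collected and are candidates. Because the Background describes sarcopenia as loss of both mass and function, an outcome built on function tests alone should be labelled as such.
4. Compare MAsS with L3-SMI only on outcomes derived from neither.

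The cost is a change of wording in the aim and the outcome definition, with no new data. The downside is fewer events. For scale, the Discussion's HCC incidence of 2–5% per year implies about 150 × 0.02 × 2 = 6 to 150 × 0.05 × 2 = 15 cases over two years before losses. The article gives no cohort-level rate for decompensation or new sarcopenia from which the number of events given up could be calculated.

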#### Secondary aims

To determine prognostic factors associated with increased mortality.To evaluate non-invasive markers for development of portal hypertension.The diagnostic performance for spleen-based assessment of clinically significant portal hypertension (CSPH) with MRI in predicting events of hepatic decompensation.To investigate the relationship between muscle composition, development of CSPH with health-related quality of life.If the diagnostic performance/robustness of the body composition profile-based assessments improves in combination with:i)data driven analysis of population data,ii)combinations of/other BCP biomarkers,iii)other relevant measurements such as blood samples or genetic compositioniv)the inclusion of multiple muscle groups in BCP analysis which allows for correcting for confounding factors such as nerve injuries.

### Ethical considerations

All recruitment and attainment of informed consent are conducted according to nationally accepted practice and in full accordance with the World Medical Association of Helsinki 2018. Data is collected and processed in accordance with the applicable General Data Protection Regulation (EU) 2016/679 (GDPR) legislation, and in compliance with the International Conference of Harmonization – Good Clinical Practice (ICH-GCP) requirements [18].

The ACCESS-ESLD study was approved by the Swedish Ethical Review Authority 2020–07215, 2021-02-23 with amendments 2022–02902-02 and 2022–06142-02 and is registered as a clinical trial (clinicaltrials.gov identifier NCT 05502198).

### Participants

Patient recruitment will take place at the Gastroenterology and Hepatology clinics at the University Hospital in Linköping, District Hospital in Eksjö and County Hospital in Jönköping. Patients with a clinical diagnosis of cirrhosis are eligible for inclusion and invited to participate by their hepatology nurse or hepatologist during clinical visits. Adult patients of both sexes will be consecutively included. The inclusion and exclusion criteria are presented in Table 1.

**Table 1 Tab1:** Inclusion and Exclusion criteria

Criteria	
Inclusion	Established liver cirrhosis according to clinical practice criteria Age ≥ 18 years Signed informed consent
Exclusion	Contraindications to perform MRI (pacemaker, ferrous metal implants/fragments, claustrophobia, extreme obesity, and/or pregnancy) Diagnosis of primary sclerosing cholangitis Diagnosis of hepatocellular carcinoma Previous liver transplant

After receiving information about the study and the opportunity to ask questions, participants will be asked to provide written informed consent, witnessed, and dated, by a member of the clinical research team. Written informed consent will always be obtained prior to study-specific procedures.

### Estimation of sample size and power calculation

One of the main objectives of the study concerns sarcopenia in patients with cirrhosis, and sarcopenia is therefore the basis for our power calculations. Previous imaging-based studies on muscle mass and composition in patients with cirrhosis have found sarcopenia to be prevalent in a range of 30 to 70% of patients [19].

At the time of the study design, there were limited numbers of studies with longitudinal follow-up of muscle loss in a somewhat comparable way. One of these studies has shown that an annual loss of muscle volume of − 3.1% (measured by computer tomography) is significantly associated with a high risk of mortality in this patient group [20]. We have previously shown that we can measure muscle volume with a precision of 0.8–1.5% (coefficient of variation) [21, 22].

To detect a change of − 3.1% in a year with a precision of 1.5% (assuming upper limit for safety) and a risk of incorrectly rejecting our hypothesis (α) of 5% and a statistical power (1-β) of 90%, would require a population size of 47. We should reach this population size, with margin, with a total population of 150 people, if about 60% will suffer from muscle loss and we take heed for loss due to e.g.*,* technical errors, study persons who choose to refrain from continued participation, and other unpredictable events that may affect data collection and its quality. A frequently used statistical power of 80% requires 35 people, and we can then assume that if our population is in the low 30% that will suffer from muscle loss, we can still expect to see differences/effects.

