### Follow-up

After inclusion and collection of baseline data, follow-up visits are performed after 6, 12, 18 and 24 months (Table 3). The study includes 5 visits (4 MR-examinations and a final follow-up visit) with 6 months interval if no liver lesions are found on MR-examination. If a nodule is defined as LI-RADS > 3, the patient has reached a significant endpoint and no further study visits will be performed (follow-up data will be collected through chart review). If a LI-RADS-3 is found on MR-examination, the time interval between subsequent MR-examinations is shortened from every 6 months to every 4 months during a 12-month period. This adds an extra MR-examination for patients with LI-RADS-3 (cumulative total of 5 MR-examinations instead of 4 during the study period) and therefore the cumulative number of visits is also increased from 5 to 6 visits (Fig. 1).

**Table 3 Tab3:** Flow chart of inclusion and follow-up visits

Procedure/data collection	Baseline (visit 1)	Follow-up (visit 2–4)	End of study (visit 5)
**Evaluation incl/excl criteria**	X		
**Informed consent**	X		
**Demography**	X		
**Medical history**	X		
**Family history**	X		
**New diagnoses**		X	X
**Health changes**		X	X
**Life-style factors**	X	X	x
**Concomitant medications**	X	X	X
**Clinical work-up**	X	X	X
**HE-assessment (ANT)**	X	X	X
**QoL questionnaires**	X	X	X
**Muscle function test**	X	X	X
**FibroScan**	X	X	X
**Blood panels**	X	X	
**Blood samples for research**	X	X	
**MR-examination**	X	X	

After end of the study period, all participants are included in regular follow-ups and HCC-screening according to clinical praxis (i.e.*,* ultrasonography every 6 months).

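### The sample-size paragraph uses the error of a single muscle-volume measurement (1.5%) as the precision of a one-year change; a two-scan change has error SD of at least 2.1%, and the calculation should be restated

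*Protocol article*

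**What the plan says.** The section on estimation of sample size and power calculation in the protocol article reports that "we can measure muscle volume with a precision of 0.8–1.5% (coefficient of variation". The following paragraph carries the upper end of that range into the calculation: a 3.1% loss is to be detected "in a year with a precision of 1.5% (assuming upper limit for safety". The error rate is "a risk of incorrectly rejecting our hypothesis (α) of 5" per cent, without saying whether the test is one- or two-sided. The result is given as a power "of 90%, would require a population size of 47", and then "A frequently used statistical power of 80% requires 35 people". The section sets these against 150 enrolled patients, of whom about 60%, or 30% in the low case, are expected to lose muscle.

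Two other places bear on the point. The primary aim asks whether "cross-sectional or temporal changes in FFMV and MFI" predict events or worsening liver function. The follow-up section plans "4 MR-examinations and a final follow-up visit", with scans at baseline and at 6, 12 and 18 months.

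**The concern.** A CV quoted for measuring a volume is the error of one measured volume. A change over a year is the difference of two such volumes and carries the error of both. The paragraph applies the single-measurement figure directly to the change and presents it as the cautious choice. For the quantity named it is not cautious: 1.5 / 2.12 = 0.71, so it understates the measurement error of the change by about 29%. The paragraph gives no SD of change and no variation between patients that could absorb the gap.

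What is at stake is mainly whether the stated basis for the sample size is correct and can be reproduced. A second consequence is for interpretation. Temporal change is a candidate predictor in the primary aim, and a reader who takes 1.5% as the error of each patient's change will trust individual changes near 3.1% more than the figures allow.

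**Working it through.** **Inputs, all from the sample-size section:** change 3.1% in a year; CV 0.8 to 1.5%; α 5% (two-sided assumed); power 90% or 80%; stated N 47 and 35.

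**1. The plan's own figures.** For a paired (one-sample) test of a mean change, N ≈ ((z for α + z for power) × SD / difference)², with an exact noncentral-t search for small N.

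| Difference | SD | N at 90%: z, t | N at 80%: z, t |
|---|---|---|---|
| 3.1 | 1.5 (as worded) | 2.5, 5 | 1.8, 5 |
| 3.1 | 2.12 (two-scan error) | 4.9, 8 | 3.7, 6 |
| 1.5 | 3.1 (roles exchanged) | 44.9, 47 | 33.5, 36 |

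Example, as worded: ((1.96 + 1.28) × 1.5 / 3.1)² ≈ 2.5. Two-sample versions of the worded inputs give 5 (z) or 7 (t) per arm at 90%. One-sided versions are no closer to 47.

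The stated pair is matched by a difference of 1.5 and an SD of 3.1. The two-sided one-sample t then needs 46.8 and 35.5 before rounding up, and 35 patients give power 0.794. The match shows that 47 and 35 do not come from the inputs as worded. It does not prove how they were obtained. If the difference really is 3.1%, N = 47 at 90% power corresponds to an SD of change of about 6.4%, a figure the article does not state.

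**2. Error of a two-scan change.** SD of change = √2 × CV, for independent errors of equal size.
- CV 1.5%: 1.414 × 1.5 = 2.12%
- CV 0.8%: 1.414 × 0.8 = 1.13%

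**3. What this means for one patient.** The 95% limit is 1.96 × SD of change.
- CV 1.5%: 1.96 × 2.12 = 4.16%, above 3.1%. The chance that a patient with a true 3.1% loss exceeds it is Φ(3.1/2.12 − 1.96) = 31%.
- CV 0.8%: 1.96 × 1.13 = 2.22%, below 3.1%. The same chance is 78%.
- Crossover: CV = 3.1 / (1.96 × 1.414) = 1.12%.

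**4. Why substituting 2.1% alone is not enough.** If the software entry was a difference of 1.5 and an SD of 3.1, putting 2.12 in place of 1.5 would lower N to 25 (90%) and 19 (80%). A larger error would then appear to need fewer patients, so the roles of the two figures must be settled as well.

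**5. Enrolment.** 60% of 150 is 90 patients and 30% is 45, against stated needs of 47 and 35. With a difference of 3.1%, 47 patients remain enough at 90% power up to a total SD of change of about 6.4%. With measurement error at 2.12%, that leaves room for a between-patient SD of √(6.42² − 2.12²) ≈ 6.1%.

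**The case against.** **It is a group calculation.** The paragraph asks how many patients are needed, not whether one patient's loss can be recognised, and the √2 factor moves the paired N only from 5 to 8. This stands. A reader might infer that the study is underpowered; the figures do not support that.

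**No patient-level rule is stated.** A reader might infer that the primary analysis will use a one-year difference, or classify patients by a 3.1% cut, and so waste the month-18 scan. The article says neither. The yearly figure matches the cited study's annual loss, and the share expected to lose muscle is an expected proportion, not a classification rule. How change is modelled belongs in the statistical analysis plan, which is not shown.

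**The gain from four scans is limited.** A slope over months 0, 6, 12 and 18 has error 1.5 / √1.25 = 1.34% per year, 37% below 2.12%. Baseline and month 18 alone already give 2.12 / 1.5 = 1.41%, and a three-scan slope to month 12 gives 1.5 / √0.5 = 2.12%, no gain. Patients with earlier events will not have all four scans. This stands, so the slope is a suggestion and its absence is not an error.

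**2.1% is the top of a range.** This also stands: at a CV below about 1.1% the single-patient conclusion reverses.

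**The CV may already refer to a difference.** The article does not say how the figure was derived. If 1.5% were the SD of a difference, the limit would be 1.96 × 1.5 = 2.94% and the √2 point would fall. The wording is against that reading, since the CV is attached to measuring volume. Even then, 47 would not follow from the inputs.

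**Conclusion.** The point holds as a fault in a stated power input. The CV of a single measurement is used as the precision of a one-year change and called safe, whereas the measurement-error SD of a two-scan change is 1.1 to 2.1%, and 2.1% at the limit the protocol chose. This is a minimum, since biological variation in change comes on top. It rests on the natural reading of the CV and on independent errors of equal size.

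At the chosen limit a 3.1% loss lies within the 95% measurement error for one patient (4.2%). At 0.8% it does not (2.2%). The effect on group sample size is small, and the enrolment target is not in question. The calculation nevertheless needs restating as a whole, because 47 and 35 do not follow from its inputs with either 1.5% or 2.1% as the SD.

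**What to change.** In the sample-size section:
- Keep 0.8 to 1.5% as the CV of a measured volume, and replace 1.5% by 2.1% where the measurement error of a yearly change is meant. If the CV already refers to a difference, say so instead.
- Restate the calculation with the difference to detect, an explicit SD of within-patient yearly change (measurement error plus between-patient variation, with its source or a range), the test, and whether it is one- or two-sided. Report the N that follows, and correct 47 and 35 or show how they arise.

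This costs a rewritten paragraph and one recalculation. It needs no new data, and 150 can stand.

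As a recommendation for the statistical analysis plan only: define temporal change from all available scans, with a landmark or joint model so that event timing does not bias the slope. Most of the gain in precision depends on the month-18 scan.
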